### Sample size

It is estimated that between 240 to 384 patients with gastroschisis will present to the seven study centres during the 2-year data collection period (
Table 4). An estimated 75% of the neonates with gastroschisis should fulfil the inclusion criteria within the context of the study sites, equating to between 180 and 288 patients in the study in total (67–109 pre-intervention and 113–179 post-intervention). A successful pre-hospital component of the study may result in more patients presenting with simple gastroschisis and hence more being eligible for study inclusion.

**Table 4. T4:** The estimated number of gastroschisis cases per month at each of the study centres.

Site	Estimated no. cases/month	Dates for pre- intervention data collection at each site (total no. months)	Minimum no. pre-intervention cases,	Maximum no. pre- intervention cases	Timeframe for intervention implementation at each site in 2019	Dates for post- intervention data collection at each site (total no. months) *	Minimum no. of post- intervention cases	Maximum no. of post- intervention cases
**Korle-Bu TH,** **Ghana**	1	Oct 2018–May 2019 (7 months)	7	7	May 13 ^th^ – June 7th	May 2019 – Oct 2020 (17 months)	17	17
**Tamale TH, Ghana**	1–2	Oct 2018–June 2019 (8 months)	8	16	June 10 ^th^ – July 5th	June 2019 – Oct 2020 (16 months)	16	32
**Komfo Anokye TH,** **Ghana**	1	Nov 2018–July 2019 (8 months)	8	8	July 8 ^th^ – Aug 2nd	July 2019 – Nov 2020 (16 months)	16	16
**University TH** **Lusaka Zambia**	2–4	Nov 2018–August 2019 (9 months)	18	36	August 12 ^th^ – Sept 6th	Aug 2019 – Nov 2020 (15 months)	30	60
**ADCH, Zambia**	1	Jan 2019–Sept 2019 (8 months)	8	8	September 16 ^th^ – Oct 11th	Sept 2019 – Jan 2021 (16 months)	16	16
**KCH, Malawi**	2–4	Dec 2018–Oct 2019 (10 months)	20	40	October 21 ^th^ – Nov 15th	Oct 2019 – Dec 2020 (14 months)	28	56
**MNH, Tanzania**	2–3	Jan 2019–Nov 2019 (10 months)	20	30	Nov 25 ^th^ – Dec 20 ^th^	Nov 2019 – Jan 2021 (14 months)	28	42
**TOTAL**	**10 – 16**	**60 months**	**89**	**145**	**8 months**	**108 months**	**151**	**239**
**No. of patients** **with simple** **gastroschisis**	**8–12**		**67**	**109**			**113**	**179**

*Each site will collect 24 months of data in total

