In this study a convenience sample has been used and hence a post-hoc power calculation has been undertaken. Utilising a two-sided Z-test it has been calculated that at 90% power and p=0.05, the study could detect a difference in mortality of 16% (95% mortality down to 79%) if the minimum number of patients were included and a difference of 12% (95% mortality down to 83%) with the maximum estimated number.

This indicates that the study is appropriately powered. Some centres within sub-Saharan Africa have achieved a mortality rate of 80% or less, suggesting it is an achievable target.

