## Data analysis

### Clinical outcomes

***Pre-post study analysis.*** Primary and secondary clinical outcomes will be compared pre- and post-intervention using chi-squared analysis for categorical variables or Fisher’s exact test if either of the groups contains less than 10 patients. For normally distributed continuous variables an unpaired t-test will be used and for non-normally distributed continuous variables a Mann-Whitney
*U* test will be used. P<0.05 will be deemed significant. Cases presenting during the 1-month implementation phase will be deemed post-intervention since the PI will be in attendance at all cases alongside the local team to assist with implementation of the protocol and training will have commenced.

***Time series analysis.*** Time series analysis will be undertaken using Statistical Process Control to distinguish significant trends and shifts in mortality from background variation during the study period
^134^.

***Multivariate analysis.*** Multivariate logistic regression analysis will be used to identify factors affecting all-cause in-hospital mortality with adjustment for confounding factors. Potential confounders include gestational age, weight, presence of co-morbidities, and ASA score at the time of primary intervention.

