### Service delivery and implementation outcomes

Regression analysis will be undertaken to evaluate the impact of the service delivery outcomes and implementation outcomes including the acceptability (AIM) score, appropriateness (IAM) score, feasibility (FIM) score and fidelity on all-cause in-hospital mortality.

In order to assess sustainability during the post-implementation phase, fidelity of the interventional bundle will be analysed using time series analysis. This will assess whether fidelity remains stable, increases or declines following implementation. Time-series analysis will also be used to assess all-cause in-hospital mortality during the post-implementation phase to determine if there is an upwards, stable or downwards trend following implementation.

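### Post-implementation mortality is to be read as upwards, stable or downwards with no interval and no inconclusive category; at 113–179 neonates an SPC chart without a signal cannot support 'stable'

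*Protocol article*

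**What the plan says.** Under Data analysis, Service delivery and implementation outcomes, sustainability in the post-implementation phase is to be assessed by time-series analysis of fidelity: "This will assess whether fidelity remains stable, increases or declines following implementation". The same approach is then applied to "all-cause in-hospital mortality during the post-implementation phase to determine if there is an upwards, stable or downwards trend following implementation".

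The method is named under Data analysis, Clinical outcomes: "Time series analysis will be undertaken using Statistical Process Control to distinguish significant trends and shifts in mortality from background variation". Chart type, signal rules and a criterion for 'stable' are not given. The 0.05 threshold in that section stands in the paragraph on the pre-post comparison, not in the one on time series.

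The Sample size section gives the expected numbers as "67–109 pre-intervention and 113–179 post-intervention" and covers the pre-post contrast only: "the study could detect a difference in mortality of 16% (95% mortality down to 79%) if the minimum number of patients were included". For the largest expected sample, the corresponding figure is 12 points, from 95% to 83%. Table 4 gives each site 14 to 17 post-intervention months, starting at different dates between May and November 2019.

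**The concern.** SPC is a tool for detecting signals. With three categories and such a tool, 'stable' is what remains when nothing signals. Read as maintained benefit, it is an equivalence-type conclusion drawn from absence of evidence. That is tolerable only if the analysis would usually detect a loss that matters.

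Sustainability is one of the eight implementation outcomes of a hybrid type 2 design that weights implementation equally with effectiveness, and scale-up is planned if the study succeeds. The principal investigator is on site for four weeks per centre and afterwards joins monthly meetings remotely, so gradual waning is a realistic way for the bundle to fail. If the chart seldom detects it, a fading effect could be described as stable.

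**Working it through.** **Inputs from the protocol.** Post-intervention neonates 113 (minimum) or 179 (maximum); pre-intervention 67 or 109; mortality 95% before, 79% or 83% after; 108 post-intervention site-months over seven sites, a mean of about 15 per site.

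**Assumptions, not in the protocol.** The shape of the loss (linear, or one mid-period step). The p-chart rules: 3-sigma limits, a run of 8 on one side of the centre line, 6 points in steady trend, centre line at the post-period mean, 15 monthly points.

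**1. The protocol's own figure.** Arcsine form of the two-sided Z-test: power = Φ(h/√(1/n₁+1/n₂) − 1.96), with h = 2·arcsin√0.95 − 2·arcsin√p₂.
- Minimum: h = 0.501, √(1/67+1/113) = 0.154, power 90.1%.
- Maximum: h = 0.399, √(1/109+1/179) = 0.1215, power 90.7%.

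The stated 16 and 12 points are reproduced. A pooled-variance test gives 86.7% and 88.1%, an unpooled one 92.9% for both. None of this concerns the trend within the post period.

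**2. Trend test, linear loss of the whole benefit.** Score test with time t uniform on 0 to 1, mean mortality p̄, total rise d:
- numerator = d·N/12
- null SD s₀ = √(p̄(1−p̄)·N/12)
- SD under the alternative s₁ = √Σ(t−½)²p(1−p)
- power = Φ((numerator − 1.96·s₀)/s₁)

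| | N = 113, 79%→95% | N = 179, 83%→95% |
|---|---|---|
| p̄ | 0.87 | 0.89 |
| numerator | 0.16×113/12 = 1.507 | 0.12×179/12 = 1.790 |
| s₀ | 1.032 | 1.208 |
| s₁ | 1.014 | 1.195 |
| power | Φ(−0.51) = 31% | Φ(−0.48) = 31% |
| missed | 69% | 69% |

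Simulation of the score and logistic Wald tests gives misses of 68–72%.

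**3. Monthly p-chart, same loss.** Simulated misses are about 78–84%, depending on chart conventions and on how cases fall across months. With constant mortality the chart still signals in about 6–8% of trials.

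One feature needs no simulation. At 113/15 ≈ 7.5 or 179/15 ≈ 12 cases a month, the upper 3-sigma limit is
- 0.87 + 3√(0.87×0.13/7.5) = 1.24
- 0.89 + 3√(0.89×0.11/12) = 1.16

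Both exceed 100%. No single month can signal a rise, even if every neonate dies; only run or trend rules can.

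**4. Other shapes of loss.**
- Abrupt mid-period loss of the same size: the trend test misses about 39%.
- Linear loss with the period mean held at 79% or 83% (63%→95%, 71%→95%): the trend test misses about 30%.
- In these two settings the p-chart misses about 57–72% in one set of simulations; in another, 68% (abrupt) and 77–79% (mean held).
- Larger linear loss, 60%→95%: the trend test misses 26% (113) or 8% (179), the chart 78% or 69%.
- Loss both large and abrupt, 60%→95% in one step: the trend test finds it almost always, and the chart misses about 35% (113) or 18% (179).

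**5. Precision if mortality is truly constant.** Half-width of the 95% CI for second half minus first half = 1.96·√(2p(1−p)/(n/2)):
- n = 113, p = 0.79: 1.96·√(0.3318/56.5) = 15.0 points
- n = 179, p = 0.83: 1.96·√(0.2822/89.5) = 11.0 points

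The planned benefits are 16 and 12 points.

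**6. Fidelity.** Power for a linear decline of k SD = Φ(k·0.289·√n − 1.96). For k = 0.5 this is 33% and 49%; for k = 1 it is 87% and 97%. Fidelity is better placed than mortality, but a moderate decline is still missed about half the time or more.

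**The case against.** The strongest reply is that no decision rule is written. A reader might infer that a non-significant test will be called stable and that a vanished benefit would then be reported as sustained. The protocol says neither. Chart rules and the exact criterion may sit in an analysis plan that is not shown, and P<0.05 is not attached to the time-series analysis. This stands: the claim can only be that the reading could be made. What the article does fix is the three-way classification, without an interval or an inconclusive outcome.

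A miss rate of 70–80% might also be taken as general. It is not. The 79% and 83% in the power calculation are whole-period rates; using them as starting levels puts mean post mortality at 87% or 89%. The pre-post test would then be significant in only about 42% of trials, and a significant benefit together with no upward trend arises in 27–28%. With the period mean held at the design value, that pair arises in 25–26%. This too stands, but it concerns mainly the regression trend test. The named method, SPC, stays weak in most settings checked.

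Sustainability also draws on fidelity, the re-scored sustainability model and surveys repeated at study end. Study limitations concedes that longer follow-up would be ideal, and the monthly meetings continue. So the mortality trend is not the only evidence, but none of this makes it able to show stability.

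**Conclusion.** The point holds in limited form and is worth acting on. For mortality, silence of an SPC chart at 113–179 neonates does not support 'stable'. Under linear loss of a design-sized benefit, about 70% of losses are missed by a trend test and about 78–84% by a monthly p-chart. For abrupt losses of that size, or linear losses with the period mean held at the design value, the trend test misses about 30–40% and the chart more than half. Only a loss both large and abrupt is usually found.

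The chart figures rest on assumed rules and all miss rates on an assumed shape of loss. Less dependent on these choices are an upper 3-sigma limit above 100% and an interval of about ±11 to 15 points, nearly as wide as the planned benefit. That a faded benefit *would* be reported as sustained is not established. The primary pre-post comparison is not affected.

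**What to change.** In Data analysis, Service delivery and implementation outcomes:

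- Replace the three-way reading by an estimate: the change in mortality and in fidelity over time since each site's own implementation, stratified by site, with a 95% CI.
- State that absence of an SPC signal will not be read as stable or as maintained benefit, and that for mortality the late-minus-early interval is expected to be about ±11 to 15 points.
- Use 'stable' only if the interval excludes a loss of benefit that the investigators specify in advance; otherwise report 'inconclusive'.
- Keep SPC charts for the monthly feedback meetings.

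The cost is wording and one model on data already collected, with no extra patients. The drawback is that the mortality result will probably be inconclusive. As an illustration only, with a margin of half the planned benefit (8 or 6 points) truly constant mortality would be confirmed with probability Φ(8/7.66 − 1.96) = 18% or Φ(6/5.62 − 1.96) = 19%. The margin is the investigators' to choose, and the protocol offers no source for one.

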## Data management

Anonymous, de-identified patient data will be entered into REDCap by the study teams. Study teams will be able to access their own patient data, but not data from other study centres. The data will be pseudo-anonymised at a local study centre level – study leads will maintain a separate, confidential list of REDCap codes with patient identifiers to permit patient follow-up and later identification if required. The principal investigator will have access to the full anonymous, de-identified dataset and other team members on the steering committee, expert advisory committee and study steering committee will have access on a need to know basis for data management and analysis purposes. At no stage will the principal investigator or any team members outside of the local study centre have access to the key to the pseudo-anonymised data. Data on REDCap is backed-up on the King’s College London secure server on a daily basis and is managed by King’s REDCap Administration Team. The principal investigator will maintain a weekly back-up of the data on two password protected, encrypted memory sticks. A data management plan has been registered and approved by King’s Data Protection Regulation team.

## Ethical considerations

Ethical approval has been gained at all participating sites. Ethical approval reference numbers: King’s College London, HR-17/18-7107; Korle-Bu Teaching Hospital, KBTH-IRB/00037/2018; Tamale Teaching Hospital, TTHERC/19/06/18/04; Komfo Anokye Teaching Hospital, CHRPE/AP/616/18; University Teaching Hospital Lusaka, 063-08-18; Arthur Davison Children’s Hospital, TRC/C4/01/2019; Kamuzu Central Hospital, P.05/18/2398; Muhimbili National Hospital, NIMR/HQ/R.8a/Vol.IX/2844.

### Patient consent

Written consent will be required from the guardian holding parental responsibility for patients included in the study (
Supplementary File 7)
^110^. Parents will be provided with an information leaflet in their own language and they will have a detailed discussion with a member of the study team to ensure they understand the potential benefits, risks and alternatives to participating in the study (
Supplementary File 7)
^110^. All parents will be informed that there is no obligation to participate and if they do agree to participate, they are free to withdraw at any stage. Patient’s legal guardians will be able to request access to their own child’s data. At the time of consent for participation in the study, consent will also be sought to openly publish their child’s anonymised data. All study team members will receive training on parental consent for research during the MDT Training Day. If any ethical issues arise during the project, they will be discussed amongst the lead investigators and study site leads, the relevant ethical committees and the study steering committee.

### Study Steering Committee (SSC)

An SSC consisting of two academic paediatric surgery consultants will independently oversee the project to ensure it is ethically sound throughout (
Supplementary File 8)
^110^. They will have access to the anonymous patient data collected in real time. If any major complications or deaths occur that may be associated with the intervention, these will be discussed and addressed between the SSC and study teams.

It is unlikely that the interventional care bundle will worsen outcomes compared to the current situation of above 95% mortality across the study centres. The main potential risk is bowel ischaemia related to incorrect application of the silo from either torsion of the vessels, use of a silo that is too small or an abdominal wall defect that is too small requiring incision under local anaesthesia
^135^. Training will be provided to avoid this complication and to recognise the early signs of bowel compromise, with techniques to remedy the situation before irreversible ischaemia and necrosis occurs. Of note, studies have shown bowel ischaemia is just as common in neonates receiving primary closure; however, in the latter, the problem cannot be visualised and remedied as easily
^54,
55^. Overall, use of a preformed silo is less invasive than the alternative of surgical interventional and general anaesthesia and hence carries less risks to the patient, especially in a low-resource environment without the availability of neonatal intensive care facilities. Insurance will be provided through King’s College London for any harm caused to patients receiving the care in the study protocol.

### Unintended consequences

Potential unintended or indirect consequences of the study, both positive and negative, must be considered.

Positive consequences may include:

•   Improved team building/ interaction/ communication with benefits for a wider range of patients.

•   Improved generic neonatal care and resuscitation skills and infection control awareness with potential benefits for a wider range of patients.

•   Development of infrastructure and supply routes required to enable delivery of neonatal PN with benefits to a wider range of patients.

•   Enhanced research capacity.

•   Enhanced CV’s and career progression amongst those involved.

•   Greater staff job satisfaction with the potential for improved retention rates.

•   Development of networks with international partners with the potential for future collaborative projects.

Negative consequences may include:

•   Potentially less time with other patients.

•   Disruption of study team members work/life balance.

•   Risk of reduced survival/increased complications in those few (5-10%) with simple gastroschisis who may have survived with primary closure in theatre if available.

•   Risk of prolonged hospital stays and resource utilisation without improved survival.

The above possible negative consequences will be discussed with study team members and a plan instigated to minimise risk. Parents will be informed both in writing and verbally of both the potential benefits and risks associated with participation in the study at the time of consent.

## Discussion

### Study limitations

•   Active involvement of the study team members in the development of the interventional bundle could result in changes being made prior to implementation of the interventional bundle. This could result in a lack of significant difference pre- and post-intervention.

•   Longer term follow-up would be ideal to assess for sustainability after study completion.

•   The in-country implementation phase is limited to 4-weeks at each site. Hence, only 1–4 patients with gastroschisis will be expected to present during this time in order to utilise the new management bundle whilst the PI and team are present. However, MDT simulation training using a gastroschisis model will permit additional hands-on training and troubleshooting.

### Dissemination of results

All study team members will be involved in the dissemination of results through local, regional, national and international conferences. The results will be submitted for open-access peer-reviewed publication in a high impact journal. Study team members who have contributed to the design, undertaking, analysis and write-up of the study will be included as authors. Other teams members who have contributed to the study, but do not fulfil authorship criteria, will be acknowledged. Following publication, the full anonymised dataset will be made openly available to the public. Where all necessary approvals have been obtained, qualitative data will be converted into a suitable format for public dissemination and deposited in the open access UK Economic and Social Data Service (ESDS).

### Study impact

The systematic review, qualitative study and Delphi process will all provide unique evidence towards optimising care for neonates with gastroschisis in low-resource settings. Each study will be submitted for publication. The interventional study will allow for that evidence to be tested in-practice across seven tertiary paediatric surgery centres in sub-Saharan Africa. The study design will enable detailed analysis of which components of the interventional bundle and implementation strategy were and were not effective. Including multiple sites in the study will determine the generalisability of the intervention and will permit a more detailed analysis of contextual factors affecting outcome.

If successful, funding will be sought to scale-up the intervention to other sites across sub-Saharan Africa and then LMICs globally using a stepped-wedge approach. This has the potential to save the lives of hundreds of neonates born with gastroschisis. Since the majority of neonates with gastroschisis typically go on to live a full and normal life, the number of DALYs averted is very high. Gastroschisis has been described as a ‘bellwether procedure’ for neonatal surgery in low-resource settings
^2^. Hence, potentially improving the care for neonates with gastroschisis could also improve outcomes for neonates with other congenital anomalies that require a similar package of neonatal surgical care. This could have a wider global health impact in light of the recent Global Burden of Disease Report findings that congenital anomalies have recently risen to become the fifth-leading cause of death in children under 5 years globally
^136^.

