### Implementation science

Implementation science is the study of methods to promote the adoption and integration of evidence-based practices, interventions and policies into routine health care and public health settings. This includes the use of evidence-based implementation strategies and theory in the project or study design and evaluation of the implementation outcomes in addition to clinical outcomes. There are eight defined implementation outcomes, as follows
^107^:

•   Acceptability: Perception amongst stakeholders that the new intervention is agreeable.

•   Adoption: Intention to apply new intervention.

•   Appropriateness: Perceived relevance of the intervention for the setting and problem.

•   Feasibility: Extent to which an intervention can be applied.

•   Fidelity: The proportion of management protocol components completed as intended.

•   Coverage: The proportion of eligible patients who actually receive the intervention.

•   Cost: Costs of the intervention, including the delivery strategy.

•   Sustainability: Extent to which a new intervention becomes routinely available/ is maintained post-introduction.

Although the above QI projects commonly describe the intervention and clinical outcomes, none have formally evaluated implementation outcomes. Such information is vital to understand which components of both the interventional bundle and the implementation strategy are effective or not. For example, if an intervention is not successful is it because the intervention itself is ineffective or is it because it was not effectively implemented and hence not used in practice. In this study, implementation science techniques will be utilised to optimise the study design, implementation of the interventional bundle and evaluation of the outcomes to optimise its success and reproducibility
^108^.

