### Outline of the interventional bundle

The interventional bundle will consist of both pre-hospital and in-hospital components. Each of these will have core components that will be consistent across the seven study centres and adaptable components for optimisation to the local context (
Table 1). The content and detail of the core and adaptable components will be further defined utilising the results of the systematic review, qualitative study and Delphi process. A summary of the drivers to achieving a reduction in gastroschisis mortality is summarised in
Supplementary File 1
^110^.

**Table 1. T1:** An outline of the core and adaptable components of the interventional bundle.

Pre-Hospital	In-Hospital
Core	
A pre-hospital management protocol will be implemented at first and second level healthcare facilities (both government and private) that refer patients with gastroschisis to the study centres. These will be identified by the study leads at each site. The protocol will include: • Covering the bowel in clear plastic • Administering intravenous (IV) fluids • Keeping the neonate warm • Transferring to the study centre as soon as possible	• Use of a standardised protocol for care. • Neonatal resuscitation and ward care including IV access, IV fluids, maintenance of normothermia, appropriate antibiotics, regular monitoring and infection control. • Gastroschisis reduction and sutureless closure using a preformed silo, or equivalent, and avoidance of neonatal anaesthesia and surgery. • Early establishment of breastfeeding and enhanced enteral feeding programme.
Adaptable	

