The method of dissemination and implementation of the pre-hospital management protocol will vary at each centre according to the optimal strategy as determined by the local team. Strategies include: • Wide dissemination of a guideline, leaflet and poster detailing the protocol with pictorial representations of the steps involved via post +/- back-up with telephone communications. • In addition to the above, site visits to selected referral centres for education and training to enhance implementation of the protocol. Visits and training will be undertaken by local MDT members and the principal investigator. • As an alternative to visiting referral hospitals, a gastroschisis study day at the study centre with MDT members from referral hospitals invited for education and training to enhance implementation of the protocol. • Dissemination of the protocol through existing government health policy pathways. • Radio and/or television campaign.	• Administration of a short period of parenteral nutrition for neonates who have survived to 7-days of life. • Maternal involvement in monitoring and basic management. • Management of neonates with gastroschisis on the neonatal ICU if available.

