***Study sites.***

The study sites include seven tertiary paediatric surgery centres as follows:
1) Korle-Bu Teaching Hospital, Accra, Ghana2) Tamale Teaching Hospital, Tamale, Ghana3) Komfo Anokye Teaching Hospital, Kumasi, Ghana4) University Teaching Hospital, Lusaka, Zambia5) Arthur Davison Children’s Hospital, Ndola, Zambia6) Kamuzu Central Hospital, Lilongwe, Malawi7) Muhimbili National Hospital, Dar es Salaam, Tanzania

The study sites were included based on the following criteria:
Presence of a local champion/ study lead who requested/ agreed to participate in the studyTertiary Paediatric Surgery Centre where patients with gastroschisis are managedAt least 1–4 cases of gastroschisis per monthAbove 90–95% mortality from gastroschisis at baseline

***Stakeholders.*** Stakeholders at micro (patient/ parents), meso (healthcare facility teams) and macro (regional/ national) levels will be incorporated, with the main interventions being at the micro-meso level. The key stakeholders are summarised in
Table 3. All members of the MDT caring for neonates with gastroschisis are included as stakeholders. The study leads from each centre have identified a lead nurse and neonatologist and/or paediatrician and have held local team meetings to discuss and contribute to the study design and protocol. The study leads, lead nurse and lead neonatologist and/or paediatrician will be invited to participate in the qualitative study and Delphi process. The principal investigator (PI) will meet in-person with the study lead, lead nurse, lead neonatologist and/ or paediatrician, hospital management and the wider MDT involved in caring for neonates with gastroschisis for a co-development meeting when in-country. This will finalise the adaptable components for the interventional bundle. All in-hospital stakeholders will be involved in the implementation of the interventional bundle and follow-up MDT meetings to monitor progress and troubleshoot.

**Table 3. T3:** Key stakeholders for the pre-hospital and in-hospital components.

Stakeholders for pre-hospital component	Stakeholders for in-hospital component

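### The protocol says the design will show which bundle and implementation components worked, but the only contrast it sets up is the whole package before versus after; component analyses can give exploratory associations only

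*Protocol article*

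**What the plan says.** The claim is in the Discussion, under Study impact: "The study design will enable detailed analysis of which components of the interventional bundle and implementation strategy were and were not effective". It carries no qualification, and the Study limitations list does not mention separating components.

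The design is described elsewhere in the article:

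- **Bundle structure (Outline of the interventional bundle).** "Each of these will have core components that will be consistent across the seven study centres and adaptable components for optimisation to the local context". Four pre-hospital and four in-hospital core items are listed in Table 1.
- **Adaptable items (Table 1).** "The method of dissemination and implementation of the pre-hospital management protocol will vary at each centre". The in-hospital options are parenteral nutrition (PN), maternal involvement and use of a neonatal ICU where there is one. PN is described as "Administration of a short period of parenteral nutrition for neonates who have survived to 7-days of life".
- **Timing (Table 4; Pre-post study analysis).** Each site has one switch from pre to post. Cases in the implementation month count as post. Site start dates run from May to November 2019.
- **Implementation package (Training; Further training and support; Sustainment stage).** The training day, the principal investigator's four weeks, the nurse specialist, the gastroenterologist and the monthly meetings are planned for every site.
- **Component data and analysis (Service delivery outcomes; Fidelity; Data analysis).** Bowel cover, pre-arrival fluids, times and PN receipt are recorded per neonate. A fidelity checklist is completed at silo application and at defect closure. Mortality is to be regressed on the service delivery outcomes, the acceptability, appropriateness and feasibility scores, and fidelity.

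**The concern.** To call one component effective and another not, a design needs neonates, sites or periods that differ in that component for reasons unrelated to prognosis. This design sets up no such difference. Core items and implementation activities arrive as a block at each site, and adaptable items follow local choice and resources.

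The remaining information is who happened to receive what. That depends on how the neonate was referred, how late it arrived and, for some items, whether it lived long enough to be eligible. A regression on such data can be run and will produce coefficients. If the report follows the Study impact sentence, those coefficients will be read as verdicts on components. The same section goes on to scale-up, so an item could gain or lose standing through an artefact of survival time.

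**Working it through.** **1. Contrasts the design assigns.** Take 7 sites × 2 periods with a separate level for each site. Every core item is 0 before and 1 after at every site, so the eight core columns are identical and have rank 1: one estimable effect, the bundle as a block. The implementation activities planned for every site follow the same pattern. Staggered site starts help to separate the bundle from calendar time, but they do not separate one component from another, because within a site everything starts together.

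**2. The protocol's own size figures (Sample size, Table 4).** Applying 75% to the case totals: 0.75 × 89 = 66.75, 0.75 × 145 = 108.75, 0.75 × 151 = 113.25 and 0.75 × 239 = 179.25. These give the stated 67–109 pre and 113–179 post. The stated 90% power reproduces with the arcsine form, power = Φ(h·√(n₁n₂/(n₁+n₂)) − 1.96), where h = 2·asin√p₁ − 2·asin√p₂:

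- 67 vs 113, 95% vs 79%: h = 0.501, Φ(0.501 × 6.486 − 1.96) = Φ(1.29) = 90.1%.
- 109 vs 179, 95% vs 83%: h = 0.399, Φ(0.399 × 8.231 − 1.96) = Φ(1.32) = 90.7%.

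The pooled-variance form gives 86.7% and 88.1%. All of this concerns the whole-package comparison; no figure in the section concerns a component.

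**3. Information for a patient-level component model.** With mortality this high, survivors are the limiting count. At the mortality levels in the power statement:

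| | Minimum | Maximum |
|---|---|---|
| Post-intervention neonates | 113 | 179 |
| Mortality | 79% | 83% |
| Survivors | 113 × 0.21 = 23.7 | 179 × 0.17 = 30.4 |
| Per term, 8 components | 3.0 | 3.8 |
| Per term, 8 components + the 4 named confounders | 2.0 | 2.5 |

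Delivery rates are not given. If a component reaches 50% to 80% of post-intervention neonates (assumption), one unadjusted two-group comparison has 80% power only for mortality differences of about 22 to 24 points (n = 113) or 16 to 18 points (n = 179). At 90% delivery, 80% power is not reached at any possible difference.

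**4. Survivor bias, PN as the example.** PN is conditional on being alive at 7 days. The Introduction reports that in LMICs most of these neonates die within a median of 4 days at a facility. Suppose PN has no effect, every neonate alive at 7 days receives it, and a fraction f of deaths occurs before then. The article does not give f, and the 4-day figure runs on a different clock, so f is an assumption. Mortality without PN is then 100%, and with PN it is (1 − f)D / (N − fD), where D is total deaths.

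| f | N = 113, D = 89.3 | N = 179, D = 148.6 |
|---|---|---|
| 0.25 | 67.0/90.7 = 73.8% | 111.4/141.9 = 78.5% |
| 0.50 | 44.6/68.4 = 65.3% | 74.3/104.7 = 70.9% |
| 0.75 | 22.3/46.0 = 48.5% | 37.1/67.6 = 55.0% |

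An inert PN course would appear to lower mortality by about 21 to 52 points. The gap shrinks if some sites do not offer PN, since survivors there join the untreated group, but its direction remains. Adjusting for gestational age, weight, co-morbidities and ASA score does not remove it, because the cause is time alive and not baseline risk.

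Fidelity has the same structure: the closure checklist exists only for neonates who live to closure.

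**The case against.** The strongest reply is that the protocol does plan component-level work. Receipt and fidelity are recorded per neonate, half the cases have a second observer, adaptations are coded separately from non-compliance, and adjustment for confounders is planned. Core items such as intravenous fluids need not be absent before the intervention or universal after it, so real variation in receipt exists. This stands: associations can be estimated, and it would be wrong to say that nothing about components can be learned.

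A reader might go further and infer that component effects are unidentifiable outright because Table 1 lists eight adaptable options (five pre-hospital, three in-hospital) against seven sites. The documents do not support that as the main argument. The count limits only a joint site-level model of all options, which the protocol does not propose. Some options are cumulative or substitutes ("As an alternative to visiting referral hospitals, a gastroschisis study day at the study centre"), the table is an outline still to be refined, and PN receipt is a patient-level record.

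A reader might also take the Implementation science section as a second instance: "Such information is vital to understand which components of both the interventional bundle and the implementation strategy are effective or not". In context, that passage concerns telling an ineffective intervention from one that was not taken up, which fidelity and coverage data do address. It needs no edit.

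Finally, it can be said that this is one Discussion sentence, that no decision rule drops a component, and that exploratory labels belong in an analysis plan. The absence of a decision rule is true and limits the consequence. But the sentence asserts a property of the design, and no analysis plan can supply a contrast that the design lacks.

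**Conclusion.** The point holds. The Study impact sentence claims more than a single-switch, uncontrolled pre-post bundle study can deliver. The assigned contrast is the package as a whole, and even that is open to changes over time other than the bundle. Component and fidelity regressions are feasible but associational: receipt is not assigned, at least two of the measures depend on having survived, and only about 24 to 30 post-intervention survivors are expected.

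The survivor count assumes that the recruitment estimates and the 79% and 83% mortality levels are met; lower mortality would give more survivors and more precision, but would not create assignment. The detectable differences and the PN illustration rest on the assumed delivery rates and timing of death shown above. The primary mortality comparison and its sample size are not affected.

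**What to change.** 1. **Study impact.** Replace the sentence with wording to this effect: *The design estimates the effect of the whole bundle as implemented, before versus after. Analyses of individual bundle or implementation components are exploratory associations and will not be used to call a component effective or ineffective.*
2. **Data analysis, Service delivery and implementation outcomes.** Label the component and fidelity regressions as exploratory in the same terms, and describe them as associations with mortality, not impact on it.
3. **Study limitations.** Add that components are introduced together within each site, that receipt is not assigned, that PN receipt and closure fidelity depend on survival, and that few survivors are expected.
4. **Implementation science.** Leave unchanged.

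This is a wording change only: no data item, sample size, primary analysis or element of care is altered. The cost is that the stated reach of the conclusions becomes less favourable.
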